## Introduction

Fifty years after its widespread recognition, a significant minority of patients with carpal tunnel syndrome continue to experience poor outcomes from treatment. Much of the current treatment is supported by inadequate or nonexistent evidence. Surgical decompression, often considered the definitive solution, leads to positive results in 75% of the cases, but leaves 8% of patients worse than before [1].

Open release is the preferred surgical procedure. Some patients referred failure to relieve symptoms after decompression surgery, and reoperation is sometimes necessary. This is consequence of incomplete release of the flexor retinaculum, scarring around the median nerve, or incorrect diagnosis [2-4]. Open release is not without complications, these produce symptoms different from those present before surgery and can be very disabling and difficult to treat. The "major" complications are rare and consists in lesion of the recurrent motor branch, severance of the palmar cutaneous branch of the median nerve or of palmar terminal branches of the median or ulnar nerves with or without neuroma, bowstringing of the flexor retinaculum, tendon or artery injuries, reflex sympathetic dystrophy. The "minor" complication are more frequent (pillar pain, loss of grip, scar tenderness or hypertrophy, wound infection, trigger finger) [5-7].

Pillar pain and loss of grip are temporary and spontaneously disappear within about 3 months, even if some authors reported the persistence of pillar pain and scar tenderness even after 2 years of follow-up [8]. Endoscopic and limited-incision techniques seem to have fewer complications than classical open surgery, but meta-analysis study was inconclusive on which is the best surgical approach [9]. However endoscopic technique provides faster relief of pain, more rapid improvement in functional abilities and earlier return to work [10].

The nonsurgical interventions with clear benefit are neutral-angle wrist splinting (with a success rate of 37%), and steroids, which show better effects when administered by local injection than orally. The initial positive response rate to injection is 70%, but there are frequent relapses as demonstrated by the 12 studies included in the last Cochrane Review [11].

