### Sample size

The main output parameter is the Symptom Severity Scale (SSS) score of the self-administered Boston Carpal Tunnel Questionnaire. The values reported in the literature assessing the cortisone treatment effect after 2 and 3 months are ranging between 1.37 - 2.3 (mean ± standard deviation: 1.6 ± 0.7). It has been estimated that a minimum number of n = 26.2 subjects for each group would be necessary to reveal a significant (α = 0.05) decrease in the SSS score from 1.6 to 2.0 with enough power (90%). If a drop-out of 4 subjects is considered, the minimum number of subjects required should be adjusted to no. = 30.

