### Data analysis

The values for each recorded parameter (NCV, CSA, BQ, VAS) will be submitted to a two-way ANOVA, with the main factors TREATMENT (cortisol vs progesterone) and TIME (baseline, 1 month, 6 months, and 12 months after the injection). The significance level will be set at *p *< 0.05. Tukey's test post-hoc analysis will be performed when necessary, in order compensate for possible type I errors.

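### The named two-way ANOVA over four visits makes poor use of women who leave; a likelihood-based repeated-measures model on all observed visits would serve the 6- and 12-month comparisons better

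*Protocol article*

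**What the plan says.** Three statements in the protocol article bear on this.

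- **Outcome (Sample size).** "The main output parameter is the Symptom Severity Scale (SSS) score of the self-administered Boston Carpal Tunnel Questionnaire". The Clinical criteria section adds that a high score means severe impairment.
- **Drop-out (Sample size).** After giving a minimum of 26.2 per group, the article continues: "If a drop-out of 4 subjects is considered, the minimum number of subjects required should be adjusted to no. = 30". It does not say whether the 4 are per group or overall. The figure of 30 is read as per group because 60 women are planned in two groups.
- **Analysis (Data analysis).** The recorded parameters, including the Boston Questionnaire, "will be submitted to a two-way ANOVA, with the main factors TREATMENT (cortisol vs progesterone) and TIME". TIME has four levels: baseline, 1, 6 and 12 months. Tukey post-hoc tests follow where needed.

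The article does not say which form of two-way ANOVA is meant, or how a missing visit is treated.

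**The concern.** The plan expects some women to leave and then names an analysis that, as usually run, makes little use of what they contributed before leaving. A classical repeated-measures ANOVA needs all four values from each woman, so one missed visit removes her altogether. An ANOVA on whatever values exist keeps her early scores, but its month-12 contrast is simply the difference between the women still measured at month 12.

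The late visits matter here. The Design of the trial section lists duration of effect, with follow-up at 6 to 12 months, as a secondary outcome. If women doing badly leave one arm more often, the mean of those who remain in that arm looks better than the mean of all women randomised to it. Such loss in the cortisone arm would hide a lasting advantage of progesterone. Such loss in the progesterone arm would suggest an advantage that is not there. Enrolling more women restores the count but does not remove this bias.

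**Working it through.** **1. The plan's own figures.** Inputs from Sample size: SSS "mean ± standard deviation: 1.6 ± 0.7", a difference of 2.0 - 1.6 = 0.4, alpha 0.05 with sidedness not stated, power 90%.

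The 26.2 reproduces as (0.7 x (1.645 + 1.282) / 0.4)^2 = 26.2, which is a one-sample, one-sided formula. The allowance is then 26.2 + 4 = 30.2, written as 30. These figures serve below only to fix the scale: SD 0.7, difference 0.4, 30 per arm, 4 leavers.

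**2. Assumptions added here, not in the article.**
- SSS scores are normal with SD 0.7 at each visit, and the arms do not truly differ.
- The correlation between the month-6 and month-12 scores is 0.5 to 0.7.
- The 4 women of 30 with the worst month-6 scores in one arm do not return for month 12. Nobody leaves the other arm.

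**3. Shift in the month-6 score among stayers.** Removing the upper fraction p = 4/30 = 0.133 of a normal distribution lowers the mean by SD x phi(z) / (1 - p), where z = 1.111 and phi(z) = 0.2153:

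0.7 x 0.2153 / 0.867 = 0.174.

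That is the large-sample value. For exactly 30 women, the expected four largest standard normal values are about 2.04, 1.62, 1.36 and 1.18, with sum 6.20. The other 26 therefore average -6.20 / 26 = -0.238, and the shift is 0.7 x 0.238 = 0.167.

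**4. Carry-over to month 12.** With equal SDs, the month-12 mean of the stayers shifts by the correlation times the month-6 shift:

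| Correlation | 30 women | Large sample | 30 women, as share of 0.4 |
|---|---|---|---|
| 0.5 | 0.5 x 0.167 = 0.083 | 0.5 x 0.174 = 0.087 | 21% |
| 0.7 | 0.7 x 0.167 = 0.117 | 0.7 x 0.174 = 0.122 | 29% |

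The month-12 contrast among the women still measured is thus biased by about 0.08 to 0.12. Its standard error is 0.7 x sqrt(1/26 + 1/30) = 0.188, so the bias is about 0.4 to 0.6 of a standard error.

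**5. The alternative in the same scenario.** A simulation of 20,000 trials per correlation gave a bias among stayers of 0.085 and 0.119. An estimate that also used each leaver's observed month-6 score, as a likelihood-based model does, had a bias of about 0.002.

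**6. Where the alternative does not help.** If leaving depended on the month-12 score itself, which nobody sees for a leaver, the shift would be the full 0.17. A likelihood-based model would not remove it. If loss were random and equal in the two arms, neither method would be biased.

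**The case against.** The strongest reply is that a journal article condenses the full protocol. The analysis set, missing-data rules and retention procedures are commonly left to that protocol or to the statistical analysis plan, and their absence here is no finding. That stands. So does the reply that the article does not say which ANOVA is meant. If a likelihood-fitted mixed model was intended, only the wording needs to change. What remains is that a method is named, and in its usual forms it is the weaker choice for a plan that expects drop-out.

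A reader might infer more than the article supports:

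- **That leavers are replaced, that their data stop being collected, or that only completers are analysed.** None of this is written. Raising the sample size for expected drop-out is standard practice and is compatible with analysing everyone as randomised. The Design of the trial section has all sixty women evaluated at every visit.
- **That the article's background shows the loss to be non-random.** The Introduction says "The initial positive response rate to injection is 70%, but there are frequent relapses", and later sections describe corticosteroid benefit as short-lived. These statements concern response and relapse. None says who leaves a trial. Outcome-related loss is plausible, but it is an assumption of this review.
- **That larger biases are to be expected.** If the roughly 30% initial non-responders (9 of 30) all left one arm and were its worst scorers, the shift would be 0.35. That is more than twice the plan's allowance and treats non-response as departure, which the article does not do.
- **That the allowance falls materially short.** If the 4 are per group, 30 - 4 = 26 against 26.2, but power on the plan's own formula is 89.8% against 90%. If the 4 are overall, 2 per group, then 28 remain and there is no gap. Correcting to 27 per group would also endorse a base figure that comes from a one-sample formula. The same inputs in a two-group formula give 2 x 26.2 = 52.5, so 53 per group one-sided, or 65 two-sided. That is a separate and larger matter.

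**Conclusion.** The point holds as an improvement to a stated method; it does not show that the trial's comparison is invalid. In its usual forms, the ANOVA either loses women with a missing visit or compares at 6 and 12 months only those still measured. With 4 outcome-related leavers from one arm of 30, the 12-month SSS contrast would be off by about 0.08 to 0.12 points, roughly a fifth to three tenths of the planning difference. This rests on SD 0.7 from the article and on three assumptions that it does not state: normal scores, a visit correlation of 0.5 to 0.7, and leaving in one arm only, driven by the observed month-6 score. Loss spread over both arms, or only weakly related to scores, would give less. The recommended model nearly removes the bias when leaving depends on observed scores. It does not do so when leaving depends on unobserved ones, which is why a sensitivity analysis belongs beside it.

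**What to change.** In the Data analysis section, replace the two-way ANOVA with a likelihood-based repeated-measures model. It should contain treatment, visit and treatment-by-visit terms, allow for correlation between a woman's own visits, and be fitted to every observed visit of every randomised woman, grouped by assigned arm. Report the treatment contrasts at 1, 6 and 12 months from that model.

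Add one sensitivity analysis in which women without a late SSS value are given an unfavourable one, so that the reader can see whether the conclusion survives loss that the main model cannot correct.

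The cost is a few lines of text and a standard analysis. No extra patients, visits or measurements are needed. The model calls for a stated correlation structure, fixed in advance, and it relies on loss being explained by observed scores. If the full protocol or analysis plan already specifies such a model, aligning the article's wording with it is enough.

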### Data analysis

The values for each recorded parameter (NCV, CSA, BQ, VAS) will be submitted to a two-way ANOVA, with the main factors TREATMENT (cortisol vs progesterone) and TIME (baseline, 1 month, 6 months, and 12 months after the injection). The significance level will be set at *p *< 0.05. Tukey's test post-hoc analysis will be performed when necessary, in order compensate for possible type I errors.

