### Electrophysiological criteria

The median and ulnar nerve conduction velocity (NCV) study is performed according to the guidelines of the American Association of Neuromuscular & Electrodiagnostic Medicine for CTS [52]. Surface recording electrodes are placed over the motor point of the abductor pollicis brevis muscle for the median nerve and over that of the abductor digiti minimi for the ulnar nerve. The reference electrode is placed over the tendon. Maximum motor conduction velocity was calculated from elbow to wrist for the median nerve and below-elbow to wrist for the ulnar nerve. Distal motor latency (DML) is measured with a distance of 7 cm between the stimulation point of the nerves at the wrist and the above mentioned muscles. DMLs are measured from the stimulus onset to the initial negative response, and amplitudes are measured from baseline to negative peak. Electrical stimuli are delivered by a constant current stimulator through bipolar surface electrodes. The sensory nerve action potentials are recorded orthodromically with stimulating ring electrodes placed around the proximal and distal interphalangeal joints. Maximum sensory conduction velocity and maximum sensory action potential amplitude (SAPa) of the median (M3, middle finger-wrist; M4 ring fringer-wrist) and ulnar (U4 ring finger-wrist) nerves are determined. The difference between U4-M4 SCV is also calculated. Skin temperature was maintained > 32°C with an infrared lamp and recorded with a digital thermometer. Neurographic values at least 2 SD above or below the mean of the normative data of our laboratory (see below) are considered abnormal. Patients are eligible for the study if electrodiagnostic studies demonstrates any one of the following: I) abnormal comparative test i.e. a difference of >10 m/s between sensory conduction velocity of the median (M4) and ulnar (U4) nerves; II) abnormal digit/wrist sensory conduction velocity (M3 < 45 m/s and/or M4 < 43 m/s) and normal distal motor latency (DML <4.3 ms) of the median nerve. In other words, we will select only patients belonging to class I and II of the electrophysiological classification of CTS severity reported by Padua et al. [53], excluding subjects with absence of the sensory action potential or delayed DML or absence of the compound muscle action potential (CMAP) of the median nerve.

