### Design of the trial

Sixty women with idiopathic mild CTS will be evaluated at before (baseline), 1, 6 and 12 months after injection.

The major outcome of this study is to determine that locally-injected progesterone may be more beneficial than cortisone in carpal tunnel syndrome at clinical level (SSS-BQ, VAS). Secondary outcome measures are:

- duration of experimental therapy, with a short (after 1 month) and long follow-up (after 6 to 12 months);

- improvement of electrodiagnostic and ultasonographic anomalies at various follow-up;

- correlation of the neurophysiologic and ultrasonographic data with clinical evaluation;

- comparison of the beneficial and harmful effects of the cortisone versus progesterone.

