## Conclusion

Peripheral nerves are able to synthesize and metabolize neuroactive steroids, as progesterone, and are a target for these molecules, since they express classical and non-classical steroid receptors [46]. Progesterone modulate the expression of key transcription factors for Schwann cell function, regulate Schwann cell proliferation and promote the expression of myelin proteins involved in the maintenance of myelin multilamellar structure, such as myelin protein zero and peripheral myelin protein 22. These actions may result in the protection and regeneration of peripheral nerves affected by different form of pathological alterations. Indeed, progesterone is able to counteract biochemical, morphological and functional alterations of peripheral nerves in different experimental models of neuropathy, including the alterations caused by aging, diabetic neuropathy and physical injury.

In our case local corticosteroid injection for CTS is no effective treatment that can stop or reverse median nerve damage and progesterone could to represent really a new therapeutic approach. Therefore the main goal of our study is to show the neuroprotective effects of the progesterone at the level of the peripheral nervous system in humans and "mild" CTS represents a good model.

The results of this trial will be presented as soon as they are available.

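### The Conclusion calls neuroprotection the main goal, but the nerve measures are secondary, and the per-parameter 0.05 rule has no error control across them

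*Protocol article*

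**What the plan says.** On the aim, the protocol article speaks with two voices. Design of the trial sets the major outcome as whether "locally-injected progesterone may be more beneficial than cortisone in carpal tunnel syndrome at clinical level (SSS-BQ, VAS"), and lists among the secondary outcomes "improvement of electrodiagnostic and ultasonographic anomalies at various follow-up". The Methods part of the Abstract has the same order. Sample size agrees: "The main output parameter is the Symptom Severity Scale (SSS) score of the self-administered Boston Carpal Tunnel Questionnaire". The closing Conclusion then states: "Therefore the main goal of our study is to show the neuroprotective effects of the progesterone". The Conclusion of the Abstract and the end of the Introduction name clinical effectiveness and neuroprotection side by side without ranking them.

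On the analysis, Data analysis states: "The values for each recorded parameter (NCV, CSA, BQ, VAS) will be submitted to a two-way ANOVA", with main factors TREATMENT and TIME. The significance level is 0.05, and Tukey's post-hoc test is used where needed as the protection against type I error.

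On what NCV contains, Electrophysiological criteria describes several recordings, including "Maximum sensory conduction velocity and maximum sensory action potential amplitude (SAPa) of the median (M3, middle finger-wrist; M4 ring fringer-wrist"). It also describes motor velocity, distal motor latency, response amplitudes and the difference between ulnar and median ring-finger velocity. The same part of the article adds input-output curve parameters, to be compared before and after treatment.

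**The concern.** A trial that is positive on SSS and negative on the nerve measures meets its goal under Design of the trial and misses it under the Conclusion. The reverse result does the opposite.

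The claim that the Conclusion ranks first also has no deciding test. Data analysis gives each recorded parameter its own test at 0.05, NCV is a label for several quantities, and no nerve parameter is singled out. Tukey's test adjusts comparisons among group and time means within one ANOVA; it does nothing about running the ANOVA on many parameters. A neuroprotection statement could therefore rest on whichever nerve parameter happens to fall below 0.05.

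**Working it through.** **The sizing figure.** Sample size gives "mean ± standard deviation: 1.6 ± 0.7", a difference of 0.4 (1.6 against 2.0), α = 0.05 and power 90%. The stated 26.2 per group is reproduced by (0.7 × (1.645 + 1.282) / 0.4)² = 26.2, a one-sided formula without the factor 2 for two groups. That is a separate matter. What counts here is that every input is an SSS quantity and none is a nerve measure.

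**Count of nerve parameters.** From Electrophysiological criteria, for the median nerve:
1. motor velocity, elbow to wrist
2. distal motor latency
3. motor response amplitude
4. M3 sensory velocity
5. M4 sensory velocity
6. M3 sensory amplitude
7. M4 sensory amplitude
8. U4-M4 velocity difference

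The input-output curves add threshold, slope and plateau for motor and sensory responses, up to six more.

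**Independent tests.** With no true effect and one TREATMENT test per parameter at two-sided 0.05:
- at least one significant in either direction: 1 − 0.95⁸ = 33.7%
- at least one significant in favour of progesterone: 1 − 0.975⁸ = 18.3%

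**Correlated tests.** The documents give no correlation, so it is an assumption. Take test statistics Zⱼ = √ρ·W + √(1−ρ)·Eⱼ, with W and the Eⱼ independent standard normal. Count how often at least one |Zⱼ| exceeds 1.96, or at least one Zⱼ exceeds +1.96 for the favourable direction. With 400,000 simulated draws for each ρ above 0:

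| Assumed ρ | Either direction | Favouring progesterone |
|---|---|---|
| 0 (exact) | 33.7% | 18.3% |
| 0.3 | 30.1% | 15.2% |
| 0.5 | 25.0% | 12.5% |
| 0.7 | 19.1% | 9.5% |
| 0.9 | 12.0% | 6.0% |
| Single test | 5% | 2.5% |

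**Sensitivity to the count.** Five parameters (for instance, leaving out the three amplitudes) give 21%, 18% and 15% in either direction at ρ = 0.3, 0.5 and 0.7. Fourteen, with the input-output parameters added, give 51% at ρ = 0, 35% at 0.5 and 14% at 0.9.

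**Effect of the fix.** One parameter named in advance returns the rate to 5%. Holm's procedure starts at 0.05 / 8 = 0.00625 and keeps the joint rate at or below 5% for any correlation. With independent tests, 1 − (1 − 0.00625)⁸ = 4.9%.

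**The case against.** The strongest reply is that the operative sections agree with one another. The Abstract, Sample size and Design of the trial all put the clinical outcome first, so the conflict is one sentence in a closing discussion. Secondary outcomes are not normally powered, and choosing among them is commonly left to an analysis plan, which is not shown here. Electrophysiological criteria mainly describes how recordings are made and who qualifies; it does not declare eight efficacy endpoints. No sentence says that one significant parameter proves neuroprotection.

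Much of this stands. It makes the point small and the error rate conditional. It does not remove the point, because the article does more than stay silent: it ranks neuroprotection first, fixes a test for each recorded parameter at 0.05, and offers Tukey's test as the safeguard, which does not reach across parameters.

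Stronger readings are tempting, and the documents do not support them:
- A reader might infer that a false neuroprotection signal is 4 to 6 times likelier than stated. No joint rate is stated, only the per-test 0.05. The multiple holds only for a common correlation of roughly 0.3 to 0.67; over 0.9 to 0 it runs from 2.4 to 6.7.
- A reader might add the treatment-by-time interaction and arrive at 36% to 51% for eight parameters. Data analysis names only the two main factors and no interaction test.
- A reader might say that forearm motor velocity counts equally with the sensory measures. The article gives no weighting at all.
- A reader might restore the hierarchy as SSS alone. Design of the trial names VAS as well.

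**Conclusion.** The concern holds in limited form. The Conclusion contradicts the outcome hierarchy set elsewhere in the article, and the stated testing rule gives no protection across nerve parameters to the claim the Conclusion ranks first.

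The size depends on three assumptions: that NCV covers about eight quantities, that one TREATMENT test is run on each, and that any single significant one would be read as neuroprotection. Under these, the joint false-positive chance lies between the ρ = 0.9 and ρ = 0 rows of the table, with no basis in the documents for choosing a point in that range. It is above the single-test rate throughout, though only modestly so at the high-correlation end. If NCV were in fact one named quantity, there would be no inflation among the conduction measures.

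The issue limits what may be concluded about the nerve. It does not touch the comparison on SSS.

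**What to change.** 1. Reword the Conclusion so that the main goal is the clinical outcome of the Abstract, Sample size and Design of the trial, with the nerve effect secondary. When doing so, keep in view that Sample size names SSS only, while the other two name SSS and VAS.
2. In Data analysis, allow a neuroprotection statement on one of two bases: a single nerve parameter named in advance, or a result that survives Holm adjustment across the nerve parameters. Label unadjusted nerve results exploratory.

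The choice of parameter is the investigators'. The U4-M4 sensory velocity difference is one candidate: it is already calculated, already an entry test, and uses the woman's own ulnar nerve as reference. Against it, entry is also possible on M3 or M4 velocity, so it need not be abnormal in every woman. The article itself also says that input-output curves show slowing in mild disease that conventional tests miss.

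The cost is wording only, with no new measurement. The downside is that an isolated significant nerve parameter can no longer support the claim.
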